#### Analysis of secondary outcomes

The secondary outcomes listed above (see “Secondary outcome measures”) will be analysed using appropriate regression models and will adjust for the baseline measure of the outcome, where possible, and centre.

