#### Exclusion criteria

The presence of any of the following exclusion criteria warrants exclusion:Known lung cancer or chronic lung disease (for example, cystic fibrosis, COPD, bronchiectasis);Has an ‘active’ diagnosis of asthma (for which any treatment has been given in the past 5 years);The patient’s LRTI warrants same day hospital admission or immediate antibiotics (note: use of delayed prescription (post-dated by at least one working day after the randomisation date) does not preclude OSAC trial participation):According to NICE guidelines, the patient warrants immediate antibiotic treatment by virtue of one or more of the following:A.Is clinically very unwell or has symptoms and signs suggestive of pneumonia, for example tachypnoea (>20 bpm), unilateral chest signs or consolidation, or hypoxia (oxygen saturation <94%) or other systemic infection, for example suspected bacteraemiaorB.Is at high risk of complications, including patients with chronic heart, chronic lung (for example, COPD, bronchiectasis and cystic fibrosis), chronic renal, chronic liver or neuromuscular disease or immunosuppression; or with complications from previous episodes of lower respiratory tract infection, for example hospital admission for pneumoniaorC.Aged over 65 years with at least two of the following criteria, or aged over 80 years with at least one of the following criteria:I.Unplanned hospitalisation within the previous yearII.Type 1 or Type 2 diabetesIII.History of cardiac failureRequires an oral or systemic antibiotic on the day of consultation to treat another infection unrelated to their acute cough, for example a co-existing cellulitis (note: use of topical antibiotics does not preclude OSAC trial participation);Recently (≤1 month) used inhaled corticosteroids;Recently (≤1 month) used short- (up to 2 weeks) course systemic corticosteroids;Currently using, or has previously (≤12 months) used systemic steroids for a cumulative period greater than 2 weeks, that is “long-term” use;Known to be pregnant, is trying to conceive or is at risk of pregnancy (for example, unwilling to take a reliable form of contraception) in the next month;Currently breast-feeding;This is not the patient’s usual practice, that is the patient is visiting or is not intending to stay with the practice for the 3 month trial follow-up period;Previously randomised into the OSAC trial;Has been involved in another medicinal trial within the last 90 days or any other clinical research study within the last 30 days;Is unable to give informed consent or complete the trial paperwork (including the symptom diary) through mental incapacity, for example major current psychiatric illness, learning difficulties and dementia;Known immune-deficiency, for example chemotherapy causing immunosuppression, asplenia or splenic dysfunction, advanced cancer or HIV infection;Patient due to receive the shingles vaccine in conjunction with the influenza vaccine;Has any of the following (A-P) known contraindications or cautions to oral steroids:Current or previous history of:A.Peptic ulcer diseaseB.Previous tuberculosis (TB)C.No previous chickenpox and known recent (≤28 days) history of close personal contact with chickenpox or herpes zosterD.Known allergy to prednisolone or other OSAC trial tablet ingredients (potato starch, lactose monohydrate, colloidal silicon dioxide, sodium starch glycolate, magnesium stearate), galactose intolerance, Lapp lactase deficiency or glucose-galactose malabsorptionE.OsteoporosisF.GlaucomaG.Suspected ocular herpes simplexH.Cushing’s diseaseI.EpilepsyJ.Severe affective disorders, for example manic depression, previous steroid psychosisK.Previous steroid myopathyL.Intention to use a live vaccine in the next 8 weeks or has received a live vaccine in the previous 2 weeks (note: assess live vaccine status by cross-checking with the British National Formulary)Current history only:M.Uncontrolled diabetes (glycated haemoglobin or HbA1C >8%)N.Uncontrolled hypertension (note: as per Responsible Clinician’s routine clinical judgement)O.Taking other interacting medication (e.g. phenytoin and anti-coagulants)P.Any other British National Formulary listed contraindication or caution (note: as per Responsible Clinician’s routine clinical judgement)Is unable to swallow tablets

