#### Secondary outcome measures

Antibiotic consumption;Duration of corticosteroid tablet use;Total duration and severity of symptoms (cough; phlegm; shortness of breath; wheeze; blocked/runny nose; chest pain; fever; muscle aching; headache; sleep disturbance; feeling generally unwell; activity disturbance), until the severity of each is scored by the participant as ‘1’ or ‘very little problem, and abnormal peak flow (defined as a peak flow reading that is not within the range of values that would be expected according to a standard predictive algorithm based on gender, height and weight);Adverse events including re-consultation for a documented illness deterioration;Patient satisfaction with treatment and intention to use the same treatment if it were to be available in the future;Clinical diagnosis of asthma, COPD, whooping cough (pertussis), or lung cancer at 3 months;Quality of life (using the EQ-5D-5L);NHS treatment and investigation costs, out-of-pocket patient and family costs, and the cost to society of time off work.

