### Screening for eligibility (the routine consultation)

Patients presenting with cough will be approached by the healthcare professional managing their clinical care (‘Responsible Clinician’) or by another member of the practice team responsible for patient identification (for example, reception staff or the ‘Recruiting Clinician’), given a short explanation of the trial, and invited to be screened for eligibility. If the patient is willing, the clinician will screen the patient for eligibility. This process includes a detailed check of the inclusion/exclusion criteria, and a routine clinical examination, of which the results and the clinician’s diagnosis will be recorded on the case report form (CRF). The routine clinical management of the patient will be completed as normal. This may include giving the patient a discretionary delayed antibiotic prescription (to be used if the patient’s condition deteriorates after 48 hours or if failing to improve after 7 days) and the discretionary use of a β-agonist (for example, salbutamol). A requirement for immediate antibiotic treatment renders the patient ineligible.

Once the patient’s eligibility is confirmed, the trial prescription will be authorised (by a GCP-trained GP) for redemption (by the Recruiting Clinician, not the patient) against a trial Patient Pack. The patient is then referred to a further interview for full recruitment and trial entry.

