### Participant follow-up

All follow-up will be managed by the trial team, who will give participants individual support throughout their follow-up period. Participants will complete the symptom diary online or on paper every day for up to 28 days or until symptoms have been completely resolved for two consecutive days (whichever is soonest). As well as recording the severity of their symptoms, completing the symptom diary includes recording peak flow measurements and whether or not any antibiotics have been taken. The patient will also record how many of the trial tablets they took on days 1 to 5, and any adverse effects during the first 7 days.

All participants will be telephoned within the first 2 days of trial entry, and then each week for 4 weeks to support symptom diary completion, collect the daily data they have recorded during the preceding week (to safeguard against potential loss of data if paper diaries are not returned to the trial centre or there are problems with the post), and to collect the weekly data on resource use and quality of life measures. These methods are similar to those successfully used (with <20% attrition) in previous studies [2,5,40,41].

Should the patient’s cough persist beyond 28 days, their permission will be sought to continue with the weekly calls, up to a maximum of 56 days, in order to establish the day on which the patient last scores their cough as “moderately bad”, and the date on which their cough is completely resolved. The 56 day cut-off point has been chosen as a pragmatic cut-off point, in order to establish the date of cough resolution for the majority of participants while taking account of the participant’s research burden, and of the trial resources. The patient will not be asked to complete any further trial paperwork after the initial 28 day period.

Participants will receive thank you vouchers worth £15 during their participation in the trial, as there is systematic review evidence that small monetary tokens increase response rates [42].

A review of participants’ primary care notes will be undertaken by the recruiting primary care site, to record NHS contacts (and their causes), prescriptions, secondary care referrals and any clinical diagnoses of asthma, COPD, whooping cough or lung cancer in the 3 months post-randomisation. This data collection will take place at least 4 months after randomisation to allow for secondary care contacts and test results to be evident in the primary care notes.

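### For antibiotic consumption the stated adjustment probably comes down to little more than centre; prespecifying the delayed prescription given before randomisation would add some precision

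*Protocol article*

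**What the plan says.** Under Analysis of secondary outcomes, the protocol article gives one rule for the whole list: the outcomes "will be analysed using appropriate regression models" and the models "will adjust for the baseline measure of the outcome, where possible, and centre". No model or covariate set is given for any single outcome.

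"Antibiotic consumption" heads the list under Secondary outcome measures and is also the first secondary research question. Participant follow-up says how it is collected: "completing the symptom diary includes recording peak flow measurements and whether or not any antibiotics have been taken".

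Three other places matter:

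- **Entry.** Screening for eligibility states: "A requirement for immediate antibiotic treatment renders the patient ineligible". The Exclusion criteria also remove anyone who needs an oral or systemic antibiotic that day for an unrelated infection.
- **Delayed prescriptions.** Screening for eligibility describes routine management at the consultation: "This may include giving the patient a discretionary delayed antibiotic prescription". The Exclusion criteria confirm this: "use of delayed prescription (post-dated by at least one working day after the randomisation date) does not preclude OSAC trial participation". The recruitment interview and trial entry come afterwards.
- **Use of baseline factors.** Randomisation is stratified by centre only. The provision to add covariates that turn out imbalanced at baseline, under Analysis of primary outcomes, is confined to the two primary outcomes. The Subgroup analyses list includes antibiotic consumption and β-agonist prescriptions, but not the delayed antibiotic prescription.

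**The concern.** A baseline measure helps when it varies between participants and predicts the outcome. Here the entry criteria remove patients who need an antibiotic on the day, so a baseline measure of antibiotic use has little room to vary. The rule then leaves roughly centre alone.

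The consultation nevertheless divides participants, before randomisation, into those who leave with a delayed prescription and those who would have to seek an antibiotic again. The article recognises the link: under Trial entry it arranges the order of first trial dose and collection of the delayed antibiotic so as to protect antibiotic consumption as an outcome. A factor that is fixed before randomisation, must be known to the site because its date affects eligibility, and bears directly on the outcome is a natural covariate. The stated rule makes no use of it.

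What is at stake is precision on the outcome closest to the trial's antimicrobial-resistance rationale.

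**Working it through.** The article states no power, rate or effect size for antibiotic consumption, so there is no figure to reproduce. The steps below ask whether omitting the covariate affects validity, and how much precision it might cost.

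**Inputs.** The number analysed is taken as 174 per arm, the retained number under Sample size calculation; applying it to this outcome is an assumption. Also assumed, because the article does not give them: *p*, the share holding a delayed prescription; *a*, antibiotic use among holders; *b*, use among the rest.

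**Variance explained.** Overall use is m = pa + (1 − p)b. A yes/no covariate explains R² = p(1 − p)(a − b)² / [m(1 − m)] of the variance of a yes/no outcome. On the risk-difference scale, adjusting multiplies the standard error by about √(1 − R²) and is worth about 1/(1 − R²) times the participants.

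- *p* = 0.30, *a* = 0.40, *b* = 0.15: m = 0.225; R² = 0.21 × 0.0625 / (0.225 × 0.775) = 0.0131/0.1744 = 0.075. Standard error × 0.962; equal to about 8% more participants.
- *p* = 0.50, *a* = 0.50, *b* = 0.10: m = 0.30; R² = 0.25 × 0.16 / (0.30 × 0.70) = 0.04/0.21 = 0.190. Standard error × 0.900; equal to about 23% more participants.
- Weak predictor, *p* = 0.40, *a* = 0.20, *b* = 0.10: m = 0.14; R² = 0.24 × 0.01 / (0.14 × 0.86) = 0.0024/0.1204 = 0.020. Standard error × 0.990; equal to about 2% more participants.

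**Chance imbalance.** The standard error of the between-arm difference in the share of holders is √[2p(1 − p)/174], which is 4.9 percentage points at *p* = 0.30 and 5.4 at *p* = 0.50. A 5-point imbalance is therefore about one standard error. It moves the unadjusted risk difference by 0.05 × (a − b): 1.25 points in the first case and 2.0 in the second. The unadjusted standard error of the risk difference with no treatment effect is √[2m(1 − m)/174]: 4.5 and 4.9 points. The shift is thus 1.25/4.5 ≈ 0.3 and 2.0/4.9 ≈ 0.4 standard errors.

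**Validity.** A simulation of 20,000 trials with no treatment effect used 174 per arm, *p* = 0.40, *a* = 0.60 and *b* = 0.10, a stronger predictor than any above (R² = 0.24 × 0.25/0.21 = 0.29). The unadjusted comparison gave a mean difference of 0.0003 and a two-sided type I error of 0.051 at the nominal 0.05. There is no sign of bias or inflation.

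**The case against.** The main objection is that this is a condensed journal article. Covariates for an individual secondary outcome commonly belong in the statistical analysis plan, which is not shown. That stands to this extent: it cannot be said that the trial's full plan omits the delayed prescription. But the article does not simply defer the matter. It states a covariate rule, and for this outcome that rule probably yields little.

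Four stronger readings are tempting, and the document does not support them.

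- *The rule contradicts the entry criteria.* It does not. The baseline measure is required only where possible, which already covers an outcome without a usable one. Nor is the baseline provably constant: coughs of up to 28 days are admitted and no listed criterion excludes antibiotic use earlier in the episode.
- *The delayed prescription is the strongest predictor available.* The article ranks no predictors and gives no rates. That it bears directly on the outcome is as far as one can go.
- *The unadjusted comparison is invalid.* Randomisation protects it, and ordinary confidence intervals already allow for chance imbalance in an unstratified factor.
- *The gain equals a fixed number of extra participants.* Those conversions hold for a risk difference. The article does not fix the model. In a logistic model, adjustment changes the target to a conditional odds ratio and does not shrink its standard error in this way.

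**Conclusion.** The point holds as a minor efficiency suggestion. For antibiotic consumption the stated rule probably amounts to little more than centre, while a legitimate pre-randomisation covariate with a direct bearing on the outcome goes unnamed. The loss is in precision only. Under assumed rates the covariate explains about 8% to 19% of the outcome variance, and about 2% if it predicts weakly, so the gain could be trivial. These figures rest entirely on the assumed prescription and usage rates, on the risk-difference scale, and, for the standard errors in points, on 174 analysed per arm.

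**What to change.** In Analysis of secondary outcomes, add one line: the antibiotic consumption model adjusts for delayed antibiotic prescription at the index consultation (yes/no, from screening data) as well as centre. If the analysis plan already says this, a cross-reference is enough.

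The cost is small. Confirm that the CRF records the item, since the article does not say so explicitly; if it does not, one yes/no field at screening is needed. If the model is logistic, state that the reported effect is a conditional odds ratio. No extra participants are required and clinical care is unchanged.

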#### Subgroup analyses

The following potential effect modifiers will be examined by formal tests of interaction: age, duration of illness (both using the median from the completed dataset), presence of wheeze on auscultation, antibiotic consumption, β-agonist prescriptions, smoking status, history of hay fever, allergic rhinitis, eczema, and diagnosis of asthma or COPD at 3 months (all yes/no). The trial is not specifically powered for these analyses; interaction tests will therefore be performed as hypothesis-generating analyses and interpretation will focus on 95% confidence intervals.

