### Sample size calculation

Since the distributions of both primary outcome variables (the duration of moderately bad or worse cough and the mean severity score of all its associated symptoms on days 2 to 4 post-randomisation) will be positively skewed, sample size calculations are based on the log-normal distribution.

The mean (standard deviation (SD)) duration of bad or moderately worse cough was taken from a previous study examining the effectiveness of prescribed antibiotics for acute LRTI [5] and estimated as 5.8 (4.1) days. The mean (SD) symptom severity score between days 2 and 4 taken from the same trial was estimated as 2.3 (1.1). Using standard formulae for the mean and standard deviation of a log-normal distribution, this corresponds to 1.555 (SD 0.637) log days (or geometric mean of 4.74 days) for the cough duration outcome and 0.73 (SD 0.454) on the log scale (or geometric mean of 2.08) for the symptom severity outcome.

To account for testing multiple primary outcomes a lower alpha was specified for the symptom severity outcome to ensure that the overall alpha for the two primary outcomes remains close to 5%. Moderately bad or worse cough has been shown to resolve within 7 days for 50% of patients, 14 days for 75% and 4 weeks for 90% of patients [5]. Therefore, since duration of cough lasts significantly longer than the period during which severity of symptoms are measured (days 2 to 4) and is capturing an element of the illness severity, duration of moderately bad or worse cough might be viewed as the slightly more clinically important outcome. For this reason alpha remained at 5% for duration of cough and was reduced to 0.1% for symptom severity.

Sample size was calculated based on a 20% reduction in the duration of cough, corresponding to a geometric mean in the active treatment group of 3.79 days (mean 1.333 log days). Allowing (conservatively) for 20% attrition, 218 participants will need to be randomised per arm to retain 174 at follow-up and achieve 90% power with a two-sided alpha of 0.05. Hence a total sample size of 436 is required.

For the symptom severity outcome, a final achieved sample size of 174 participants in each arm will provide 89% power to detect a reduction in symptom severity score between days 2 and 4 of 20%, corresponding to a geometric mean of 1.66 units in the active group (mean 0.51 log units) with a two-sided alpha of 0.001.

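### Splitting age and illness duration at the sample median makes the interaction tests less efficient than continuous terms would, if effect modification is roughly linear (minor)

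*Protocol article*

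**What the plan says.** The Subgroup analyses section of the protocol article lists potential effect modifiers to be examined by formal tests of interaction. Two of them are numeric: "age, duration of illness (both using the median from the completed dataset"). The others are described as yes/no. No continuous form of either numeric interaction is given.

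The section is candid about the status of these tests: "The trial is not specifically powered for these analyses; interaction tests will therefore be performed as hypothesis-generating analyses". It adds that "interpretation will focus on 95% confidence intervals". It states no interaction effect size, no interaction power, and no distribution for age or illness duration.

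**The concern.** A median split treats everyone on one side of the cut as alike and separates near-identical patients who fall just either side of it. If the steroid effect rises or falls gradually with age or with length of illness, most of that gradient within each half is thrown away. The cut is also set by who was recruited and not by a clinical threshold, so the two halves would fall elsewhere in another sample.

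What is at stake is precision. The plan concedes low power and rests interpretation on confidence intervals, and those are the intervals that the split widens. A real gradient would be more easily missed, although the same data could estimate it better with no extra patients.

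**Working it through.** **Reproducing the plan's own figure.** Inputs from Sample size calculation: "this corresponds to 1.555 (SD 0.637) log days"; an active-arm mean of 1.333 log days, so a difference of 1.555 − 1.333 = 0.222; and "achieve 90% power with a two-sided alpha of 0.05".

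n per arm = 2 × (1.960 + 1.282)² × 0.637² / 0.222² = 173.0, rounded up to 174. Then 174/0.80 = 217.5, rounded up to 218. This matches the plan ("218 participants will need to be randomised per arm to retain 174 at follow-up"), so N = 348 analysed is used below.

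**Information kept by the split.** Let r be the correlation between a covariate and its own above/below-median indicator. If modification is linear, the split keeps a fraction r² of the information, the interval widens by 1/r, and the noncentrality of the test is multiplied by r. The covariate shapes are assumptions, because the article gives none. The skewed case is a log-normal duration truncated at the 28-day entry limit.

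| Assumed covariate | r | r² | Information lost | CI widening (1/r) |
|---|---|---|---|---|
| Uniform | 0.866 | 0.75 | 25% | 1.15 |
| Normal | 0.798 | 0.64 | 36% | 1.25 |
| Right-skewed, truncated | 0.787 | 0.62 | 38% | 1.27 |

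Truncated-normal age distributions gave losses of 31 to 34%, and several truncated skewed durations 34 to 38%. An untruncated exponential would lose 52%, so a strongly skewed duration could fall outside the range.

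**Power.** Two-sided 5% is inferred from the 95% intervals, since no separate level is stated. Power after the split is Φ(r × δ − 1.960), where δ is the noncentrality of the continuous test; the opposite tail is negligible. For 80% power δ = 2.802, so the split gives Φ(0.866 × 2.802 − 1.960) = 68% (uniform), 61% (normal) or 60% (skewed).

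| Power, continuous | Points lost: uniform | normal | skewed |
|---|---|---|---|
| 90% | 9.8 | 16.5 | 17.7 |
| 80% | 12.1 | 19.1 | 20.3 |
| 70% | 12.4 | 19.1 | 20.1 |
| 50% | 10.3 | 15.4 | 16.1 |
| 40% | 8.5 | 12.5 | 13.1 |
| 30% | 6.3 | 9.2 | 9.6 |
| 20% | 3.8 | 5.6 | 5.8 |

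**A benchmark on the plan's scale.** Suppose the treatment effect differs between the two halves by as much as the planned 20% effect, −ln 0.8 = 0.2231. For equal halves the interaction standard error is 4 × SD/√N.
- Cough duration: 4 × 0.637/√348 = 0.1366. The noncentrality is 0.2231/0.1366 = 1.634 and split power is 37%. Dividing 1.634 by r gives 1.886 (uniform) to 2.076 (skewed), so continuous power is 47 to 55%.
- Symptom severity: 4 × 0.454/√348 = 0.0973. The noncentrality is 2.292 and split power is 63%. The continuous test has 2.647 to 2.913, so 75 to 83%.

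The benchmark uses the sample-size section's log-scale SDs. The Analysis section plans a Cox model for duration and a linear regression for severity with no log scale named, so these powers are illustrative. For the linear regression the ratio 1/r does not depend on the outcome's scale; for the Cox model it is an approximation.

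**Validity.** A simulation with no interaction (348 patients) rejected in 4.8% of runs with either method.

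**The opposite case.** If the true effect is a step exactly at the median, the split is the better test. When it has 76% power its noncentrality is 2.666. The continuous test then has r × 2.666 = 2.309 (uniform) or 2.128 (normal), which gives 64% or 57%; simulation gave about 60%.

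**The case against.** The strongest reply is that little depends on these tests. They are declared exploratory, no primary or secondary conclusion rests on them, and the false-positive rate is unaffected. That stands, and it sets the severity.

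The rule is also fixed in advance and does not look at outcome or allocation. A reader might infer from the phrase about the completed dataset that a favourable cut could be searched for, or that the tests are invalid. The text supports neither: the median is a single determined value and gives roughly equal groups. Nor are the halves meaningless outside the trial, because the median can be reported in years or days. What remains is that the cut has no stated clinical basis.

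The size of the loss is conditional, and it shrinks as power falls, so the larger figures should not be attached to very weak interactions. Continuous modelling brings its own assumption, and under a step at the median it would lose a similar amount. This also stands. However, the article gives no reason to expect a step at a point set by recruitment.

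Finally, the section does not define duration of illness. Elsewhere the article uses the phrase for illness during follow-up. Reading it here as time before entry is an inference, supported by the entry criterion on length of cough.

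**Conclusion.** The point holds as a minor matter of efficiency. Against a linear continuous term, the median split loses about 25 to 38% of the information on the interaction and widens its 95% confidence interval by about 15 to 27%. It costs about 10 to 20 points of power where the continuous test would have roughly 40 to 90%, and about 4 to 10 points where it would have 20 to 30%.

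These figures assume roughly linear modification, covariate shapes from uniform to moderately right-skewed, and a two-sided 5% test. None of these is given for the interaction tests in the article. A reader might go further and take a 10 to 20 point loss as certain, or think that the trial's main conclusions are weakened. The article supports neither: the loss depends on an unstated interaction size and shape, and the primary analyses do not use the split.

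**What to change.** In Subgroup analyses, replace the median rule with wording along these lines: the treatment-by-covariate interaction will be tested with age and illness duration before randomisation as continuous terms, on a scale fixed in advance (for example, log for duration); the treatment effect with its 95% confidence interval will be reported at pre-stated values of each; results by median split will be shown for description only. Add one prespecified spline or plot to check linearity, with a statement of how it will be used. This also settles what duration of illness means.

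The cost is a sentence or two of wording, with no new patients; length of illness before entry must be available as a number of days. Completed recruitment is no obstacle. Because the code-break is withheld until the primary outcome analysis is confirmed complete, the change can be made blind to allocation. The drawback is the linearity assumption and the lower power if the true effect is a step at the median.

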#### Secondary research questions

We will also: 1) assess the effects on antibiotic consumption; 2) estimate the cost-effectiveness from the perspectives of the NHS, patients, and society; 3) compare the burden, severity and duration of abnormal peak flow and LRTI symptoms; 4) compare adverse events including any new symptoms or worsening of existing symptoms, re-consultations for a documented deterioration in illness and serious adverse events; 5) investigate if participants’ subjective or objective response to oral steroids is associated with a clinical diagnosis of asthma or COPD; and 6) assess participants’ satisfaction with treatment and intention to consult for future similar illnesses.

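### Two listed effect modifiers, antibiotic consumption and a 3-month asthma or COPD diagnosis, are post-randomisation outcomes, so treatment effects within their strata are not protected by randomisation (minor).

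*Protocol article*

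**What the plan says.** In the protocol article, Subgroup analyses opens with "The following potential effect modifiers will be examined by formal tests of interaction". The list runs from age, illness duration and wheeze on auscultation to "antibiotic consumption, β-agonist prescriptions, smoking status, history of hay fever, allergic rhinitis, eczema, and diagnosis of asthma or COPD at 3 months". Nothing in that section separates variables known at entry from those that arise later. It adds that "interaction tests will therefore be performed as hypothesis-generating analyses and interpretation will focus on 95% confidence intervals".

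Two of the listed variables appear elsewhere as outcomes. Secondary outcome measures begins with "Antibiotic consumption;Duration of corticosteroid tablet use" and later includes "Clinical diagnosis of asthma, COPD, whooping cough (pertussis), or lung cancer at 3 months". Among the Secondary research questions, the first concerns the effect of treatment on antibiotic consumption. The fifth asks whether "response to oral steroids is associated with a clinical diagnosis of asthma or COPD".

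**The concern.** A subgroup comparison keeps the benefit of randomisation only if the subgroup is defined by something treatment cannot change. If treatment influences who takes antibiotics or who is later diagnosed with asthma or COPD, then the prednisolone and placebo participants within a stratum are differently selected. Their difference mixes the treatment effect with that selection.

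At stake is the reading of two exploratory results: whether prednisolone helps less or more in people who took antibiotics, and whether it helps more in people whose asthma or COPD had not been recognised at entry. The second bears directly on secondary question 5.

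**Working it through.** **Timing of the two variables, set side by side**

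| | Antibiotic consumption | Asthma or COPD diagnosis |
|---|---|---|
| Role in Subgroup analyses | effect modifier, yes/no | effect modifier, yes/no |
| Role in Secondary outcome measures | outcome | outcome |
| When recorded (Participant follow-up) | daily diary after entry, up to 28 days | notes review covering the 3 months after randomisation |
| State at entry | need for immediate antibiotics excludes the patient (Screening for eligibility) | known COPD and active asthma excluded (Exclusion criteria) |
| What drives it afterwards | a delayed prescription is for use on deterioration after 48 hours or no improvement by 7 days (Screening for eligibility) | the article gives no rule; persisting cough, or its relief, could plausibly influence it |

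No section restricts either variable to a value fixed before randomisation. For antibiotics the order can even be reversed, because use may follow from the day 2 to 4 severity or the persisting cough being analysed.

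**Illustration of size (assumed mechanism)**

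Inputs from Sample size calculation: mean severity 2.3, SD 1.1, a 20% reduction, 174 analysed per arm.

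The plan's log-scale figures reproduce:
- SD = √ln(1 + (1.1/2.3)²) = 0.454
- mean = ln 2.3 − 0.454²/2 = 0.730

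Model, with no true effect modification:
- log severity Y = 0.73 + 0.454·Z + ln(0.8)·T, where Z is standard normal and T = 1 for prednisolone
- logit P(antibiotic) = a + b·(Y − 0.73)

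The values of a and b are assumptions. A slope b = 3 means the odds of antibiotic use rise exp(3 × 0.454) = 3.9-fold per SD of severity. A slope b = 1 means 1.6-fold. The true geometric mean ratio is 0.80 in everyone. Results by numerical integration:

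| a | b | Use, placebo v active | Ratio, non-users | Ratio, users | Interaction ratio |
|---|---|---|---|---|---|
| −1.5 | 0 | 18% v 18% | 0.800 | 0.800 | 1.000 |
| −1.5 | 1 | 19% v 16% | 0.805 | 0.806 | 1.001 |
| −1.5 | 3 | 25% v 16% | 0.830 | 0.846 | 1.020 |
| −0.5 | 1 | 38% v 33% | 0.808 | 0.808 | 1.000 |
| −0.5 | 3 | 41% v 30% | 0.840 | 0.849 | 1.010 |

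Under the strong link the true 20% reduction shows as 17% and 15%, or as 16% and 15%.

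The standard error of the log interaction with 174 per arm is the square root of the sum, over the four arm-by-stratum cells, of within-cell variance divided by cell size. It is about 0.11 for a = −1.5 and 0.09 for a = −0.5. The spurious log interactions are 0.020 and 0.010, so at most about one-fifth of a standard error.

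**Stronger or different mechanisms**
- With log-odds of 2 per SD (7.4-fold), simulated ratios are 0.85 in non-users and 0.88 in users (a = −1.5), or 0.83 and 0.87 (a = −2.5). The interaction ratios are 1.04 and 1.05.
- Suppose treatment has no effect on severity but directly lowers antibiotic use, and an unmeasured factor drives both use and severity. Simulated stratum ratios are then 1.02 and 1.03 (log-odds shift −0.5) or 1.04 and 1.05 (shift −1.0), where the truth is 1.00.

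The size therefore depends on the mechanism assumed. No comparable figure is offered for the 3-month diagnosis, because the article gives nothing on its frequency or determinants.

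**The case against.** The strongest reply is that the analyses are declared unpowered and hypothesis-generating, to be read through confidence intervals, and that no primary or confirmatory claim rests on them. This stands as a limit on the consequence. It does not remove the fault: the label speaks to power and multiplicity, and an interval around a biased estimate carries the bias with it.

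Second, the diagnosis can be defended as a marker of disease already present but unrecognised, since known COPD and active asthma are excluded, clinicians and participants are blinded, and question 5 is framed as an association. This has force. What remains is that Subgroup analyses treats a variable ascertained after treatment as an effect modifier.

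Some stronger readings are tempting, but the documents do not carry them:
- *The tests will produce a false interaction.* In the strong-link illustration the distortion is mainly attenuation in both strata, and the interaction is barely moved. Larger distortions need still stronger assumed links.
- *The trial expects prednisolone to alter antibiotic use.* The article poses this as a question, not an expectation.
- *β-agonist prescriptions share the fault.* They may be given at the index consultation. The article does not date them for this analysis, and that definition can properly sit in the analysis plan.
- *Splitting age and illness duration at the median is an error.* The cut is prespecified and does not depend on allocation. It costs some efficiency and causes no bias.

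**Conclusion.** The point holds for two variables, antibiotic consumption and the 3-month asthma or COPD diagnosis, and it is minor. The article fixes both as effect modifiers while also treating both as outcomes recorded after randomisation. Within-stratum comparisons therefore lack the protection of randomisation and may be biased.

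That conclusion rests on the documents alone. The size does not: the strength of the link between severity and antibiotic use is assumed, and the documents do not show that treatment changes either variable. If antibiotic use is related neither to treatment nor to the outcome, the bias is nil. The primary analyses and the sample size are unaffected.

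**What to change.** Amend the wording of the subgroup analysis:
- Limit tests of effect modification to variables fixed before randomisation.
- Drop antibiotic consumption as a modifier, or replace it with whether a delayed antibiotic prescription was issued at the index consultation (yes/no). The article says such prescriptions may be given but not that their issue was captured at baseline. Confirm this first; if it was not recorded, simply drop the variable.
- Report the 3-month asthma or COPD diagnosis as a descriptive association answering secondary question 5, stating that it was ascertained after treatment. Do not present it as a subgroup treatment effect.
- Keep both variables as secondary outcomes, as planned.

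The cost is a change of text and the loss of one exploratory contrast. No further recruitment is needed and the primary analyses stay as they are.
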